### Interventions

All patients participating in the study will receive behavioral therapy according to German clinical guidelines which recommend the treatment programs THAV and ScouT. The entire duration of the trial will comprise a minimum of 16 child sessions and four parent sessions and a maximum of 24 child sessions and six to nine parent sessions (see “Trial design”). The child sessions will take place on a weekly basis. In both the experimental and control group, participants will be treated with social competence training, consisting of two therapeutic programs: (1) Therapy Program for Children with Aggressive Behaviour (THAV) [4] and (2) Social Computer-Assisted Training for Children with Aggressive Behaviour Problems (ScouT) [7]. Both programs are based on evidence-based international treatment manuals, in particular the Coping Power Program [57] and Cognitive Behavioral Therapy for Anger and Aggression in Children [58].

#### THAV

THAV is a modularized therapy program for children with aggressive behavior aged 6 to 12 years. In a randomized control trial and in a within-subject design, significant moderate effects were found in terms of parent-rated peer-related aggression [5, 6]. The program is organized in five modules with separate components [4]. The modules of the training are: (1) assessment, psychoeducation and development of a therapeutic relationship; (2) social cognitive interventions; (3) anger control training; (4) social problem solving and skills training; and (5) termination and relapse prevention. These five modules are subdivided into a total of 11 treatment units, which are introduced individually as needed. The goals of the social cognitive interventions are to identify and reduce anger-inducing cognitions (*anger thoughts*), identify basic dysfunctional ideas (*thought traps; for example, “I have to be the best of everyone”*), and develop empathy *(“take another perspective!”)*. The anger control training addresses impulse control *(“control your anger!”)*, whereas the purpose of the social problem solving and skills training is to help patients develop and evaluate alternative solutions for a problem situation, and to train them in non-verbal and verbal skillful behavior, including role play*,* video feedback, and role reversal. Self-management, therapy homework assignments, and interventions in the real-life setting *(“Can you manage that in the real world?”)* with self-reinforcement are added in each of these components.

Additionally, a “magic forest game” is used, in which all modules are integrated as a game in which the child has to cope with different tasks which train different aspects of helpful social cognitions, anger control, social cognitive problem solving and behavioral social skills.

In the sessions for parents/caregivers and teachers, the child’s target problems are identified, together with his/her competences and the coercive interaction process. Problem-maintaining social interactions are addressed in each of the modules by interventions that aim to modify these interactions. These interventions include teaching the parents/caregivers how to define social rules, how to communicate effective commands, how to coach the child in social problem situations, how to use methods for rewarding the child (e.g., token systems) when the child shows prosocial behavior, and how to use appropriate methods of punishment (e.g., time-outs) when the child shows aggressive behavior. Additionally, these sessions aim to identify and modify parental dysfunctional thoughts about their child, about their own aggressive behavior, impulse control, and conflict management.

The modularized structure allows for an individual treatment plan, based on the individual difficulties of the patient, e.g. misperception and misinterpretation of social situations, impaired empathy, limited prosocial emotionality or lack of social problem-solving skills. At the beginning of the treatment, an individual behavior problem list is elaborated with the patients’ parents/caregivers. Based on that description and the clinical judgment, an individual treatment plan, consisting of the THAV elements described above, is developed, using a clinical decision-making flowchart [4].

#### ScouT

In Addition to THAV, ScouT will be included in the treatment according to clinical evaluation.

ScouT is an individually delivered, computer-assisted social skills training intervention for children with aggressive behavior aged 6 to 12 years [7]. It combines different cognitive-behavioral methods (e.g., modeling via video sequences and animated cartoon characters, role plays with therapist feedback, homework assignments). The main components are video vignettes of five peer-related conflict situations in which the protagonist is confronted with (1) disappointment, (2) verbal aggression, (3) physical aggression, (4) non-acceptance of responsibility, and (5) depreciation. The work with each video vignette follows a problem-solving approach [59]. The participant (a) first describes the conflict situation shown in the video (including exploring one’s own thoughts, feelings, and actions in such a situation); (b) chooses one of four alternative reactions of the protagonist, which best represents his/her typical reaction (socially competent, socially unassertive, verbally aggressive, physically aggressive); (c) watches a video showing the solution chosen, followed by an exploration of possible thoughts and feelings of both interaction partners and of possible consequences of the behavior, as well as similar conflict situations in his/her daily life; (d) watches a video sequence showing the consequences of the reaction chosen (and of other possible reactions); (e) identifies the best solution for the conflict situation; and (f) transfers it to a real conflict that he/she has experienced in the past.

Therapy homework assignments are an integral part of THAV and ScouT. In the control group, the children and families will complete a paper-and-pencil homework assignment in the form of a self-observation sheet between two therapy sessions. In both groups, homework assignments may comprise reporting on problematic situations in which the child shows aggressive behavior or implementing newly developed strategies during the sessions (Figs. 2, 3 and 4).

**Fig. 2 Fig2:**
[figure not shown]
AUTHARK smartphone app (version 2.0), Main navigation [56]

**Fig. 3 Fig3:**
[figure not shown]
AUTHARK smartphone app (version 2.0), Video diary [56]

**Fig. 4 Fig4:**
[figure not shown]
AUTHARK smartphone app (version 2.0), EMA [56]

### AUTHARK smartphone app

Children and their families in the experimental group will use the AUTHARK app to complete their therapy homework assignments. The AUTHARK app is strongly based on the contents of the THAV and ScouT programs and contains the following functions: (1) a video diary, (2) a momentary assessment function assessing the child’s cognitions, affects and behavior, (3) a training function, (4) a memory function, (5) an information function, and (6) a reinforcement system. The main character from THAV and the ScouT program, Till Taff, also guides the child through the app. For example, he asks the questions in the video diary or asks the child for advice in the training function. The contents of the video diary, the training function and the information function differ according to the patient’s disorders (e.g. depression, ADHD, oppositional and aggressive behavior). These individual settings can be adjusted by the therapist. In this trial, we will focus on oppositional and aggressive behavior. The different functions of the app are described in greater detail below.

The *video diary* contains questions that the child is required to answer through short video recordings. The questions prompt the child to report his / her experiences according to a behavioral analysis (e.g. Did you experience a difficult situation today? What happened? What did you think in this situation? How did you feel in this situation? What did you do or say? What happened afterwards?). If the child has not experienced a difficult situation during the day, he/she is asked about his/her most enjoyable experience of the day in similar manner.

The *momentary assessment function* measures the intensity of basic emotions (happiness, anger, sadness, disgust, and fear). In addition, disorder-specific cognitions, emotions or behaviors can be defined by the therapist and integrated into the assessment. The frequency of the assessment can be adjusted by the therapist.

The *training function* offers the opportunity to practice and improve social skills including problem-solving skills by displaying fictional situations in which the child takes on the role of the expert and helps the character Till Taff in the app to solve a conflict (i.e. gives Till Taff advice).

The *memory function* reminds the child to start his/her therapy homework assignment. Furthermore, the child is asked to report how successful he/she was in implementing the therapy homework using the video diary or, if he/she was unsuccessful, what he/she struggled with.

The *reinforcement function* comes in the form of a virtual store, in which the child can “buy” clothes and accessories for the app’s main character. The coins for the store can be earned within each function.

#### Treatment fidelity

Treatment fidelity will be ensured by (i) training in manualized treatment procedures, (ii) a structured protocol completed by therapists after each session, and (iii) supervision of behavioral therapy by senior supervisors, either face-to-face or by telephone. All treatments will be supervised after every four treatment sessions, including a review of at least two videotaped sessions.

#### Participant timeline

The individual study duration per patient is between five and seven months. Measurements will take place according to a specific schedule. The trial consists of three general parts: a screening process, the intervention period, and the follow-up assessment. Through an initial investigation using standardized telephone screening, a broad assessment of the inclusion and exclusion criteria will be conducted. Shortly after this initial investigation, the pre-treatment measurement (T1) will occur, which involves a detailed examination of the inclusion and exclusion criteria. After being randomized to the experimental or control group, all patients will undergo a first treatment phase (1), consisting of eight patient sessions and two to three parent/caregiver sessions, followed by an intermediate assessment (T2). Subsequently, another treatment phase (2) will be carried out, followed by a main assessment (T3). Non-responders to the treatment (significant symptoms of OD/CDD at T3 based on the clinician-rated parent interview (ILF-EXTERNAL) [53] and on the parent rating (SCL-DBD) from the DISYPS-III [43]) will participate in a third treatment phase (3), followed by a final assessment (T4). Responders to the treatment (no significant symptoms of ODD/CD at T3) will terminate the study and take part in a first follow-up assessment (T3) eight weeks after their last session. After one year, every family will be asked to complete a follow-up survey (T5).

Therefore, four study visits (T1-T4) will take place for all children and parents/caregivers in order to complete assessments. Additionally, there will be 16 study visits for all children and four to six study visits for all parents/caregivers (treatment phases 1 and 2). Within the group of non-responders after T3, there will be a further eight visits for children and two to three visits for parents/caregivers (treatment phase 3).

At the main assessment points (T1, T3/T4), the primary outcome (THA) and the secondary outcomes will be assessed. At the intermediate assessment (T2), the primary outcome and symptoms of ODD/CD as well as comorbid conditions will be assessed using only parent- and child-report questionnaires and without a clinical interview. The primary outcome will additionally be assessed every two weeks, as the therapist will rate the children’s THA using the Adherence Questionnaire (Fig. 5).

**Fig. 5 Fig5:**
[figure not shown]
SPIRIT Figure

#### Informants

The following informants will be considered for assessment: unblinded clinician, parent/caregiver, patient, and teacher. The unblinded clinician will be a member of the project staff who is involved in diagnostics or in therapy (but not in the family being assessed), or will be a child and youth therapist working at the School for Child and Adolescent Cognitive Behaviour Therapy (AKiP). He/she will be aware of the treatment condition and the time of the assessment. The parent may be the biological parent or the child’s guardian and will be involved in the treatment. The patient is the child participating in the study/treatment. The teacher is the child’s schoolteacher, preferably the class teacher with the main responsibility for the child’s school routine. Teachers of patients treated in the control group will remain blinded, as the paper-and-pencil method will not be implemented during school hours.

However, children in the experimental group will be asked to complete an ecological momentary assessment also during school (e.g. at break times). In these cases, teachers may recognize that pupils are in the experimental group.

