### Allocation

Participants will be randomly assigned to either the treatment condition including the AUTHARK app [56] (*n* = 35) or the active control condition, which includes treatment without the AUTHARK app but with paper-and-pencil homework assignments (*n* = 35). We will use computerized block randomization with a block size of 4 and random selections from all 6 permutations. Allocation will only take place after the participants have completed the initial screening, fulfilled all the inclusion criteria and gave their written consent (patients, parents and teachers). The participants will be randomized by the Principal Investigator [name]. The staff members who are also responsible for the recruitment and the initial diagnostics will request randomization. In return, [name] will send a digital answer form to the same staff member, containing the group allocation (experimental or control group). The staff member will then inform the therapist and the family about the treatment intervention.

Due to the nature of the intervention, it will not be possible to blind trial participants, parents/caregivers, and therapists to allocation. However, the parents/caregivers and patients will be blind regarding the specific hypotheses.

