##### Secondary outcomes

As a secondary Outcome, we will analyze the quantity (relative ratio) and the overall quality rating separately. Additionally, the percentage of tokens received from the therapists for homework compliance will be considered as a secondary outcome measure.

Further secondary outcomes listed below will be assessed at T1 (baseline) and at T3 or T4:Parent-, teacher-, and patient-rated symptoms of ODD/CD, which will be assessed using the respective rating scales: the parent-, teacher-, and patient-rated DISYPS-III Symptom Checklist for Disruptive Behavior Disorder (SCL-DBD parent, SCL-DBD teacher, SCL-DBD patient (ages 11–18)) [43]. Reliability and validity as well as the sensitivity to change of these scales have already been proven in German samples [43].Clinician-rated symptoms of ODD/CD using the Structured Interview for Disruptive Behavior Disorder (ILF-EXTERNAL), which is part of the comprehensive Structured Interview for Children and Adolescents according to ICD-10 and DSM-5 from the DISYPS-Systems (DISYPS-ILF) [53].Overall behavioral and emotional problems assessed using the total score of the German version of the Child Behavior Checklist for ages 6–18 (CBCL/6-18R-total) [44], the total score of the German version of the Teacher’s Report Form for ages 6–18 (TRF/6-18R-total) [45], and the total score of the German version of the Youth Self Report for ages 11–18 (YSR/11-18R-total) [46]. Reliability and validity as well the sensitivity to change of the German versions of these scales have been demonstrated in several studies [44].Triggering and maintaining components of aggressive behavior (social-cognitive information processing, impulse control, social skills, and reactions to the social environment) assessed using the parent- and patient-rated Questionnaire on Aggressive Behavior in Children (FAVK parent, FAVK patient (ages 9–12) [47].Parent-rated satisfaction with the treatment, assessed using the modified German version of the Client Satisfaction Questionnaire (ZUF-8-M parent), and patient-rated satisfaction with the treatment, assessed using the modified German version of the Client Satisfaction Questionnaire (ZUF-8-M patient) [61], which has been shown to be reliable, valid, and sensitive to change [62].

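### The clinician who rates ODD/CD symptoms is told the arm without a stated reason, which lets the rater's own scoring bias into one secondary outcome and one of the two parts of T3 responder status

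*Protocol article*

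**What the plan says.** The Informants section lists an unblinded clinician among the four informants and states: "He/she will be aware of the treatment condition and the time of the assessment". It describes this person as project staff "involved in diagnostics or in therapy (but not in the family being assessed), or will be a child and youth therapist working at the School" (AKiP). The exclusion of anyone involved with the assessed family is attached to project staff. It is not repeated for AKiP therapists.

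Under Allocation, the nature of the intervention is given as the reason why "it will not be possible to blind trial participants, parents/caregivers, and therapists to allocation". The assessing clinician is not in that list. The same section describes how allocations travel: "The staff members who are also responsible for the recruitment and the initial diagnostics will request randomization". The allocation form goes back to that staff member, who then tells the therapist and the family.

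The clinician's rating is used in two places:

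- Secondary outcomes lists clinician-rated ODD/CD symptoms, measured with the ILF-EXTERNAL interview.
- Participant timeline bases non-response at T3, and so entry to the third treatment phase, on the ILF-EXTERNAL and the parent SCL-DBD together. The inclusion criteria section says that the corresponding two criteria are evaluated again at T3.

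The Discussion treats bias from families and from treating therapists. It mentions a blinded evaluation only for homework adherence, and only for a later main study.

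**The concern.** Patients, parents and treating therapists must know the arm, and the Informants section accepts that teachers of app-arm children may find out. The assessing clinician is the one symptom informant for whom nothing in the intervention forces disclosure in both arms. Both arms receive the same THAV/ScouT treatment and differ in how homework is done and recorded, which an ODD/CD symptom interview does not need to know. The plan nevertheless fixes that the rater will know, and it offers neither a reason nor a safeguard.

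Two things are at stake. The first is the between-arm comparison of clinician-rated ODD/CD symptoms. The second is T3 responder status: a rater who expects one arm to do better could score borderline children differently by arm. The share entering the third phase, and so the treatment received before T4, could then differ between arms for a reason unrelated to symptoms. The trial is also meant to supply variance estimates for a confirmatory trial, so an avoidable rater effect would be carried forward.

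**Working it through.** **Is the disclosure forced?** Three statements, side by side:

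1. Allocation: blinding is impossible for participants, parents/caregivers and therapists because of the nature of the intervention. The Discussion narrows the last group to treating therapists.
2. Informants: a project-staff rater may not be involved with the family being assessed. Such a rater is therefore not a treating therapist of that family, and the reason in (1) does not reach this person. For an AKiP therapist the text is silent, so a treating therapist as rater is not ruled out.
3. Informants: the rater will know the arm.

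So (3) does not follow from (1). It is a stated choice, not a detail left to another document.

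**Which n to use for an illustration.** The Sample size section recommends about 30 per arm and expects 10 to 15% dropout. 30/(1 − 0.10) = 33.3, rounded up to 34, and 30/(1 − 0.15) = 35.3, rounded up to 36. The stated 35 per group fits. About 30 per arm would be analysable.

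**Effect on the secondary outcome.** Assumptions, none from the documents: no true difference, a two-sided 5% comparison of two means, and a rater shift of b SD in favour of one arm. With SE = √(2/n) in SD units,

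P(reject) = 1 − Φ(1.96 − b/SE) + Φ(−1.96 − b/SE).

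At n = 30, SE = √(2/30) = 0.258.

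| b (SD) | b/SE | Calculation | P(reject), n = 30 | P(reject), n = 35 |
|---|---|---|---|---|
| 0 | 0 | 0.025 + 0.025 | 5.0% | 5.0% |
| 0.1 | 0.387 | 0.058 + 0.009 | 6.7% | 7.0% |
| 0.2 | 0.775 | 0.118 + 0.003 | 12.1% | 13.3% |
| 0.3 | 1.162 | 0.212 + 0.001 | 21.3% | 24.1% |

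The exact t-test at n = 30 gives 6.7%, 11.9% and 20.8%.

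**Effect on T3 status.** Further assumptions: a child enters phase 3 only if positive on both measures, 50 to 70% are positive on each, and the two are bivariate normal with correlation 0.3 to 0.6. The clinician's threshold is shifted by b SD in one arm.

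| Positive on each | Correlation | b = 0 | b = 0.2 | Difference |
|---|---|---|---|---|
| 50% | 0.3 | 29.8% | 25.8% | 4.0 points |
| 50% | 0.6 | 35.2% | 31.0% | 4.2 points |
| 60% | 0.3 | 40.6% | 36.0% | 4.6 points |
| 60% | 0.6 | 45.7% | 41.2% | 4.5 points |
| 70% | 0.3 | 52.8% | 48.0% | 4.8 points |
| 70% | 0.6 | 57.3% | 52.7% | 4.6 points |

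In an arm of 35 this is 0.040 × 35 = 1.4 to 0.048 × 35 = 1.7 children.

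**How many interviews can still be masked?** Trial status gives a recruitment start in October 2019, planned completion in May 2022 and a protocol date of 6 April 2022. T3 follows 16 weekly child sessions. Sixteen weeks before the protocol date is mid-December 2021, so children who started before then could already have had T3. From mid-October 2019 that is about 26 of the roughly 31 months to mid-May 2022. The pace of recruitment is not given, so the share of interviews already done is unknown, but it is probably large.

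**The case against.** The strongest case against the point has five parts.

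- **Masking removes only part of the bias.** The ILF-EXTERNAL is an interview with parents, who know the arm and take part in the treatment. A masked clinician would still score their accounts. This stands: only the clinician's scoring increment is removable. A reader might infer that masking would make this an unbiased symptom measure, and the documents do not support that.
- **Not every rater is shown to be outside the family's care.** One might read the Informants section as saying that no rater ever treats the family. It says so for project staff only. This stands as a correction of scope. It does not weaken the case, because the silence on AKiP therapists is a gap that the same wording can close.
- **It is not free.** The trial is a small, unfunded, single-centre pilot, and the staff who do the initial diagnostics receive the allocation form. Keeping the arm from the rater needs some reassignment of people, and no staff numbers are given. This stands, but no new assessor category and no extra visit are needed.
- **Consequences are limited.** The primary outcome does not use this rater, and the Time factor in its planned analysis, as listed, ends at T3. Hypothesis 2 does not name the ILF-EXTERNAL, and T3 status also needs the parent rating. All of this stands. It rules out the stronger inference that the primary comparison is compromised by this choice.
- **The figures are assumed.** The study is exploratory, without a formal power calculation, and plans mixed models or generalized estimating equations rather than a t-test. This stands: the percentages show how sensitive a comparison of this size would be, not what will happen.

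Open disclosure and pilot status lower the weight of the point. They do not supply a reason for telling the rater the arm.

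**Conclusion.** The point holds in a limited form. The article makes the ILF-EXTERNAL clinician aware of the arm, its reason for not blinding does not cover an assessor outside the family's care, and project-staff raters are by rule such assessors. The clinician's own scoring bias can therefore enter one secondary outcome and one of the two components of T3 responder status. Bias from the parents' answers would remain under any masking.

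The size is unknown. Under the assumed shifts of 0.1 to 0.3 SD, the false-positive rate at 30 per arm would be about 7% to 21% instead of 5%. A shift of 0.2 SD would move fewer than two children in an arm of 35 across the T3 rule, given the assumed prevalences, correlations and a both-measures rule. Neither result is an estimate for this trial.

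This is a cheap improvement, not a defect that undermines the trial. Which clinical rule should decide entry to the third phase is not judged here.

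**What to change.** For T3 and T4 interviews still to come, state that:

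- the rater, whether project staff or AKiP therapist, neither treats the family nor requested or received its allocation, and is not told the arm (knowledge of the time point can stay);
- families are asked at the start of the interview not to mention how homework was recorded;
- the rater records a guess of the arm afterwards, and agreement beyond chance is reported;
- the report gives, by arm, which interviews were masked and which were not, with a sensitivity analysis of the ILF-EXTERNAL outcome by masking status.

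Interviews already done are reported as unmasked, with that named as a limitation.

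Cost: some reassignment and scheduling constraint in a small team, and one added item on the interview form. Accidental unmasking will happen at times and is recorded. The outcome will mix masked and unmasked ratings, and masking will go with later calendar time, so the sensitivity analysis can only be descriptive.
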